### Randomisation

With a stratified block randomisation method, a 440-case randomisation arrangement was carried out by an independent statistician according to the sequence generated with SAS software; this lists a serial number from 001 to 440 corresponding to consecutive allocation (with a randomisation scheme). Each centre receives consecutively coded drugs. All of the drugs provided by the pharmaceutical company will be numbered with a label according to the randomisation schedule.

### Blinding

This trial is a double-blind trial. The first level is for the case number corresponding to groups (group A, group B), and the second level is for the group corresponding to intervention (the test and placebo groups). The numbers are kept in opaque sealed envelopes. The double levels of blinding are sealed separately, and given to the leader and the sponsor of the clinical research. Emergency letters are sent to each of the centres, saved with the test drug, and properly preserved until the end of the trial. Treatment assignments will not be revealed and are blinded to the patients and investigators (including statisticians) until the entire study is completed. Code-breaking should only occur with the permission of the research centre leader in exceptional circumstances when serious adverse events happen and knowledge of the actual treatment is absolutely essential for further management of the patient, and a report should be submitted to the leader of the trial within 24 hours. For the first level of unblinding, before statistical analysis, the blind code will be disclosed to group A and group B. For the second level of unblinding, group A and group B will be disclosed to the test placebo groups in a summary meeting.

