### Recruitment

A total of 440 Chinese patients who fulfill the screening criteria will be recruited at eight large comprehensive hospitals in China: 1) West China Hospital of Sichuan University, 2) Affiliated Hospital of Chengdu University of TCM, 3) The First Affiliated Hospital of Heilongjiang University Of Chinese Medicine, 4) Affiliated Hospital of Jiangxi University of TCM, 5) Shanxi Provincial Hospital of TCM, 6) The First Affiliated Hospital of Guangxi University of Chinese Medicine, 7) Gansu Provincial Hospital of TCM and 8) Affiliated Hospital of Changchun University of Chinese Medicine. Each centre will recruit 55 patients through posters in local hospitals.

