### Sample size calculation

According to the results of Phase II clinical trial, the response rates of SQTX Granule and placebo were 0.51 and 0.33, respectively. Assuming the response rates for TCM and placebo were 0.5 and 0.35, the sample size was calculated under the setting of alpha = 0.05 and beta = 0.80. Taking into account a drop-out of 15%, the sample size needs to be 150 cases for each group. A total of 440 patients will be recruited in this trial, including 330 cases for the SQTX Granule group and 110 cases for the placebo group in a 3:1 ratio.

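### With 3:1 allocation, opening the A/B code before analysis identifies the SQTX Granule arm by size, so the second-level seal cannot keep the statisticians blinded

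*Protocol article*

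**What the plan says.** The Blinding section of the protocol article describes a code in two layers. The first links case numbers to group A or B, and the second links A and B to test drug or placebo. The layers are sealed separately and opened at different times: "For the first level of unblinding, before statistical analysis, the blind code will be disclosed to group A and group B", and then "For the second level of unblinding, group A and group B will be disclosed to the test placebo groups in a summary meeting". The section also says that patients and investigators, expressly counting the statisticians among them, remain blinded until the whole study is complete.

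The Sample size calculation section sets the allocation: "A total of 440 patients will be recruited in this trial", with "330 cases for the SQTX Granule group and 110 cases for the placebo group in a 3:1 ratio". The Randomisation section adds "With a stratified block randomisation method, a 440-case randomisation arrangement was carried out by an independent statistician", so the realised group sizes will stay close to that ratio.

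The Data management section says that the data are locked after a blind review and cannot be changed afterwards. It does not say outright whether the lock comes before the first-level code is opened.

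Nothing in the article masks the group sizes or restricts who knows the ratio.

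**The concern.** An A/B label keeps an analyst blind only if nothing visible in the data separates A from B. Equal allocation usually meets that condition. With 3:1 allocation it fails, because the number of patients under each code is the first thing the analyst sees and the protocol itself says which arm is the larger.

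The second layer exists to keep treatment hidden between the two openings, which is the period of the statistical analysis. If the counts already give the answer, the plan describes a safeguard it does not have. A reader of the results could be told that the analysis was blinded when in effect it was not. Any choice still open in that period could then be made with the arms known.

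**Working it through.** **Inputs.** Total 440, ratio 3:1 and drop-out 15%, all from Sample size calculation (the last from "Taking into account a drop-out of 15%, the sample size needs to be 150 cases for each group"; the 150 per group is not used here). Centre size 55, from Recruitment ("Each centre will recruit 55 patients through posters in local hospitals").

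**Step 1: reproduce the plan's group sizes.** 440 × 3/4 = 330 and 440 × 1/4 = 110, exactly as stated.

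**Step 2: sizes after loss.** 330 × 0.85 = 280.5 and 110 × 0.85 = 93.5, so about 280 against 94. Equal proportional loss leaves the ratio at 3:1.

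**Step 3: could size mislead the analyst?** Let X be the number of active patients with data, binomial with 330 trials and probability 1 − d(active). Let Y be the number of placebo patients with data, binomial with 110 trials and probability 1 − d(placebo). X and Y are taken as independent. The analyst is misled or left undecided if X ≤ Y, with probability Σ over y of P(Y = y) × P(X ≤ y).

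| Loss, active | Loss, placebo | Expected sizes | P(X ≤ Y) |
|---|---|---|---|
| 15% | 15% | 280.5 / 93.5 | about 7e-107 |
| 30% | 0% | 231 / 110 | about 8e-43 |
| 40% | 0% | 198 / 110 | about 1e-22 |
| 50% | 0% | 165 / 110 | about 7e-10 |

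The first row uses the plan's own drop-out. The other three are assumed extremes, to show how far the result can be pushed.

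**Step 4: break-even.** With no loss on placebo, expected sizes are equal when 330 × (1 − d) = 110, so d = 1 − 110/330 = 66.7%. About two thirds of the active arm would have to be lost, with none lost on placebo, before the counts stopped pointing to the active arm.

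**Step 5: a single centre.** 55 × 3/4 = 41.25, so about 41 against 14. Even under simple 3:1 randomisation, which is looser than the planned blocks, the probability of 27 or fewer active patients among 55 is about 3e-5. The list from one centre is enough.

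**Step 6: set the timing against the counts.** The A/B list is opened before analysis, and the A/B key at the summary meeting. From steps 1 to 5 the list carries the key with it. In effect there is one unblinding, and it takes place before the analysis starts.

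**The case against.** The arithmetic is hard to contest. The dispute is over how much harm follows, and there the other side has a good case.

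- **Data handling.** A reader might infer that outliers and withdrawals could be handled with the arms known. The article does not support that. Data management provides for a blind review and then a lock with no later changes, and a review called blind naturally precedes any code opening, although the order is not spelled out. The section on other criteria already says how withdrawn patients are treated, including those who stop for poor efficacy after half the course. Data analysis defines FAS and PPS. Rules for outliers commonly sit in the analysis plan, which is not shown.
- **Test choice.** A reader might also infer that the plan leaves the analyst to choose between ANOVA and a rank test. Data analysis names both, joined by and, not or. The sentence before it assigns tests by type of data, and the same split is a fair reading here. The wording is loose, since it does not say which test applies to each primary score, but it declares no choice at the analysis stage.
- **Scope.** It would go too far to say that the trial's blind fails. Patients and site investigators stay blinded during treatment, which matters most for patient-reported scores, and the first code is sealed during conduct and blind review. Nor does the article support a charge of sponsor influence: the Design section says that the funder has no responsibility for analysis or interpretation.
- **Meaning of completion.** If the study counts as complete once follow-up ends, the promise to statisticians might be read as already met when the first code opens. That does not rescue the second seal, which is meant to last until the summary meeting and has no purpose other than to cover the analysis.

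These points limit the consequence. They do not alter the fact that the A/B code cannot conceal 330 from 110.

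**Conclusion.** The point holds in a limited form. Opening the first-level code identifies the arms with near certainty (error about 7e-107 at the planned drop-out, and still about 7e-10 with half the active arm lost and none of the placebo arm). The second-level seal, and the statement that statisticians remain blinded through to completion, therefore describe a property that the design does not have.

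The exposure is confined to analysis choices made between A/B disclosure and the summary meeting. If those choices are already fixed in an analysis plan that is not shown, the practical risk is small, but the Blinding section would still misdescribe the blind.

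This rests on three assumptions: the analyst knows the published ratio; study completion includes the analysis, as the timing of the second opening implies; and the lock precedes the first opening, as Data management suggests. If the lock came later, the exposure would be wider. This should be corrected, but it does not threaten the conduct of the trial.

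**What to change.** Amend the Blinding section to state that the following are fixed and documented before the first-level code is opened:

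1. the database lock described under Data management;
2. membership of FAS and PPS;
3. the between-group test for each of the two primary scores (IBS-QOL and IBS-SSS);
4. the analysis programs.

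State also that, because of the 3:1 ratio, analysts are regarded as unblinded from that opening, and correct the sentence on statisticians to match. The cost is a few lines of text and a dated record of the sequence. Kits, sites and patients are unaffected. Recruitment was under way when the article was submitted, so the order could still be set before any code was opened.

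Splitting the larger arm is optional. The independent statistician could reissue the list as four codes of 110 (330 = 3 × 110 active, plus 110 placebo), and the fixed program would be run for each code against the other three. That removes the size clue at the price of recoding and four runs, but it adds little. It presupposes the same frozen program, and the output may point to placebo anyway: at the assumed response rates of 0.50 and 0.35, the standard error of a difference between two codes is √[(0.50 × 0.50 + 0.35 × 0.65)/110] ≈ 0.066, so placebo is expected about 0.15/0.066 ≈ 2.3 standard errors below each active code.

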### Western medicine diagnostic criteria for IBS-D

Diagnosis of IBS-D is established according to the Rome III criteria
[11,12], mode listed in Table 
2.

**Table 2 T2:** Mode of irritable bowel syndrome (IBS)

**Question**	**Score**
A) In the last 3 months, how often did you have hard or lumpy stools?	0 Never or rarely
	1 Sometimes
	2 Often
	3 Most of the time
	4 Always
B) In the last 3 months, how often did you have loose, mushy or watery stools?	0 Never or rarely
	1 Sometimes
	2 Often
	3 Most of the time
	4 Always
**Mode**	**Definition**
IBS-C	A > 0 and B = 0
IBS-D	A = 0 and B > 0
IBS-M	A > 0 and B > 0
IBS-U	A = 0 and B = 0

Diagnostic criteria*:

Recurrent abdominal pain or discomfort** at least three days/month in the last three months associated with two or more of the following:

1. Improvement with defecation

2. Onset associated with a change in frequency of stool

3. Onset associated with a change in form (appearance) of stool

*Criteria fulfilled for the last three months with symptom onset at least three months prior to diagnosis

**‘Discomfort’ means an uncomfortable sensation not described as pain.

In pathophysiology research and clinical trials, a pain/discomfort frequency of at least two days a week during the screening evaluation is recommended for subject eligibility.

### Diagnostic criteria for TCM syndrome differentiation

The TCM diagnosis of liver-spleen disharmony and diarrhea syndrome is based on the Guidelines for Clinical Research of New Chinese Medicine
[20].

For diagnosis with liver-spleen disharmony and diarrhea syndrome, patients will have both of the primary and at least two of the secondary symptoms listed in Table 
3, as well as the TCM signs for the tongue and pulse.

**Table 3 T3:** Traditional Chinese medicine (TCM) diagnostic criteria

**Category**	**Symptoms and signs**
Primary symptoms	1) Abdominal pain or discomfort, 2) Diarrhea
Secondary symptoms	1) Chest/flank or abdominal distension, 2) Diarrhea aggravation related to emotional tension, depression or anger, 3) Belching, 4) Decreased appetite, 5) Frequent sighing, 6) Fatigue
TCM signs for the tongue	Pink tongue, white/thick/greasy tongue coating
TCM signs for the pulse	Wiry pulse

### Inclusion criteria

• Diagnosis of IBS-D according to Western medicine

• Diagnosis of liver-spleen disharmony and diarrhea syndrome according to TCM

• Aged between 18 and 65 years old

• Able to understand and sign a written informed consent

### Exclusion criteria

• Diagnosis of IBS-C, IBS-M or IBS-U according to Western medicine

• A history of previous abdominal surgery

• Other organic diseases causing abdominal pain and diarrhea

• History of usage of other medication for IBS-D during the last week

• Patients taking any medication for other diseases which would impact the trial

• Pregnant and lactating women

• Patients who have an allergic constitution or are allergic to the trial medicine

• Patients with serious primary diseases of the heart, liver, kidney, blood system or endocrine system, and patients with tumours or AIDS

•Mentally or legally disabled patients

### Other criteria

Withdrawal of participants:

• Patients are determined as requiring withdrawal based on disease progression, allergic reactions, serious adverse events, or poor efficacy

• Serious complications

• Unblinding individuals for any reasons

• Voluntarily quitting

• Unable to complete the scheduled follow-up

Reasons for withdrawing patients would be noted in Case Report Forms (CRFs), and the last data would be included in data analysis.

Note: 1) Patients cured in a course of treatment are not regarded as cases for withdrawal.

2) Patients withdrawn due to poor efficacy after a half course of treatment (14 days) are regarded as not recovered but not withdrawn, and they would be included in the Full Analysis Set (FAS) and the Per Protocol Set (PPS).

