### Data analysis

Statistical analysis will be conducted based on an intention-to-treat (ITT) principle. All subjects who were treated with at least one dose of the study drug and had at least one clinical observation after starting the treatment comprise FAS. All treated subjects without any major protocol deviations comprise PPS. The statistical analysis will be performed using the SAS 8.1 software (SAS, Cary, NC, USA). The statistical significance is defined as a two-sided *P*-value of < 0.05. Baseline differences among the groups will be assessed with the use of the one-factor analysis of variance or the Mann-Whitney *U-*test for measurement data and the χ^2^ test or the Wilcoxon test for enumeration data. For categorical variables, a χ^2^ test or Fisher’s exact test will be used. The changes from baseline to endpoint of treatment in scores will be assessed with the use of a paired *t*-test for measurement data and a signed rank test for enumeration data. Comparisons between groups will be conducted by using an analysis of variance (ANOVA) and a rank test.

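### Unblinding and safety events are listed as grounds for withdrawal with the last data analysed, and nothing lets a patient stop study drug yet stay under observation to Day 28

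*Protocol article*

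**What the plan says.** All of the grounds stand under one heading, Withdrawal of participants, in the Other criteria section of the protocol article.

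- Clinical grounds that depend on a judgement: "Patients are determined as requiring withdrawal based on disease progression, allergic reactions, serious adverse events, or poor efficacy".
- Grounds with no qualifier: serious complications, and "Unblinding individuals for any reasons".
- Grounds of another kind: voluntary quitting, and inability to complete the scheduled follow-up.

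One data rule covers them all. The reason goes into the case report form, and "the last data would be included in data analysis".

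Two notes reclassify particular early stops. Note 1: "Patients cured in a course of treatment are not regarded as cases for withdrawal". Note 2: "Patients withdrawn due to poor efficacy after a half course of treatment (14 days) are regarded as not recovered but not withdrawn"; these patients enter both analysis sets. Neither note covers a safety stop or a code-break.

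Under Data analysis: "Statistical analysis will be conducted based on an intention-to-treat (ITT) principle". The full analysis set takes in patients who received at least one dose and "had at least one clinical observation after starting the treatment comprise FAS". On timing: "The changes from baseline to endpoint of treatment in scores will be assessed". The percentage symptom-score reduction under Secondary outcome is computed from the Day 0 and Day 28 scores.

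**The concern.** Stopping study drug and leaving the study are different events. A patient who has an allergic reaction, or whose code is broken to manage a serious event, may need to stop the granule. Neither event in itself prevents later completion of the IBS-QOL and IBS-SSS. The withdrawal list treats such a patient like one who has quit, and analyses whatever was last recorded.

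An intention-to-treat comparison needs the outcome at the planned time as well as the patient in the denominator. Here the outcome can be replaced by an earlier value after a stop that may itself be related to treatment. If safety stops differ between arms, the comparison shifts. An analysis plan written later cannot recover Day 28 values that were never collected, so the collection rule belongs in the protocol.

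**Working it through.** **Reading the sections together**

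1. Other criteria states both the grounds for withdrawal and the data rule, so the point does not rest on silence about missing data.
2. Notes 1 and 2 show that the authors set special handling for some early stops. They gave none to safety stops or unblinding. Dropout of participants adds only misdiagnosis, forbidden treatment, no medication taken and no evaluable records.
3. Blinding allows a code-break only in exceptional cases, when a serious adverse event has occurred and the assignment is essential for care. The unblinding ground therefore adds few patients, but they are patients with serious events, and no further judgement is asked for before they are withdrawn.
4. Intervention sets treatment at 28 days. For a patient withdrawn before then, the last recorded value precedes the planned end of treatment, whether it was carried forward or taken at the withdrawal visit.

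**Illustrative size**

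The article gives no rate of safety stops, so there is no plan figure to reproduce. The allowance of 15% drop-out (0.15 × 440 = 66 patients) is not split by reason.

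Inputs:
- Planned response rates of 0.50 (SQTX) and 0.35 (placebo), a difference of 15 percentage points, and arms of 330 and 110, all from Sample size calculation.
- Assumed, not in the documents: safety-stop proportions pT (SQTX) and pC (placebo) of 1% to 5%.

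Patients affected:
- SQTX: 0.01 × 330 = 3.3 to 0.05 × 330 = 16.5.
- Placebo: 0.01 × 110 = 1.1 to 0.05 × 110 = 5.5.

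Scenario A: the last data count as no response, but at Day 28 these patients would have responded at the planned rates. Shift in the difference = -0.50·pT + 0.35·pC.

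| pT | pC | Calculation | Shift (points) |
|---|---|---|---|
| 1% | 1% | -0.0050 + 0.0035 | -0.15 |
| 5% | 5% | -0.0250 + 0.0175 | -0.75 |
| 5% | 1% | -0.0250 + 0.0035 | -2.15 |
| 1% | 5% | -0.0050 + 0.0175 | +1.25 |

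Scenario B: the last data on SQTX keep the on-drug rate of 0.50, but off drug these patients would have fallen to 0.35 by Day 28. Only the SQTX arm is affected. Shift = (0.50 - 0.35)·pT = 0.15 × 0.01 = +0.15 points, to 0.15 × 0.05 = +0.75 points.

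The largest shift relative to the planned difference is 2.15 / 15 = 14%. With equal stop rates in scenario A it is 0.15 / 15 = 1% to 0.75 / 15 = 5%.

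**The case against.** The strongest reply is that the article never says assessment ends at withdrawal. Withdrawal may be from drug only, or just a disposition label: inability to complete follow-up is a separate ground, and Note 2 calls the same patients both withdrawn and not withdrawn. The last-data rule could mean a carried-forward value, an assessment at withdrawal, or simply that data up to that point are kept. For an early stopper, the endpoint of treatment could be the end of that patient's own treatment; only the symptom-score reduction, a secondary outcome, fixes Day 28. Visit procedures may be in the full protocol, and the flow chart and schedule are not shown.

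The ambiguity is real, so the point is put as the natural reading and not the only one. It does not remove the point. The grounds and the data rule are stated, safety stops share a list with quitting, and nothing in the article separates stopping drug from leaving.

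A reader might infer more than the documents support:

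- **That these patients are excluded from the analysis.** They are not. One observation after starting treatment keeps a treated patient in the full analysis set.
- **That every allergic reaction or serious adverse event forces withdrawal.** Those grounds apply when withdrawal is judged necessary.
- **That safety information is lost.** Adverse events are to be recorded throughout the study, and severe ones reported within 24 hours.
- **That most of these patients could be measured at Day 28.** Nothing in the documents shows this, and some will have had serious events.
- **That the rule favours SQTX.** No direction is established: an early value can hide later recovery or later relapse off drug.

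The scenarios are also fairly open to criticism. They use response rates whose definition Sample size calculation does not give, while the primary outcomes are IBS-QOL and IBS-SSS scores.

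**Conclusion.** The point holds as a low-priority improvement. On the natural reading, unblinding and safety stops take a patient out of the study, and an earlier value replaces the end-of-treatment outcome, which sits poorly with the stated intention-to-treat principle.

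The number affected is unknown and probably small, since the Discussion describes phase II as free of significant adverse events and code-breaks are confined to exceptional cases. Under the assumed 1% to 5% stop rates, the planned 15-point difference moves by between -2.15 and +1.25 points. The extreme needs 5% stops on SQTX against 1% on placebo, every stopper counted as a non-responder, and all of them otherwise responding at the planned rate. This indicates scale for a response outcome; it does not estimate bias in the two primary scores. No bias in a particular direction is shown. Confidence is medium, because withdrawal and last data each allow a milder reading.

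**What to change.** Add a Note 3 to Other criteria, in the style of Notes 1 and 2, to this effect:

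- Unblinding, a serious complication, or an allergic reaction or serious adverse event judged to require it is a recorded reason to stop study drug, not to leave the study.
- Scheduled visits continue through Day 28 and follow-up where feasible, unless consent is withdrawn.
- The full analysis set uses the observed Day 28 value. The last data are used only when no Day 28 value exists.
- The date of any code-break is recorded, and IBS-QOL and IBS-SSS scores collected after it are flagged.

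The cost is one protocol note and a case report form instruction, using visits already planned. The downside is a few extra patient contacts and some patient-reported scores given with knowledge of treatment, hence the flag. Trial status reports recruitment as on-going at submission, so the note could still apply to patients not yet withdrawn.

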### Dropout of participants

• Misdiagnosis

• Using forbidden drugs or treatments in the course of the trial

• Taking no medication during the trial

• No evaluable records after medication

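### Entering withdrawn patients with their last recorded scores can bias the primary IBS-SSS and IBS-QOL comparison in either direction, and the article leaves unclear whether dropouts stay in the full analysis set

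*Protocol article*

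**What the plan says.** Under Other criteria, the article lists grounds for withdrawal. They include "withdrawal based on disease progression, allergic reactions, serious adverse events, or poor efficacy", serious complications, any unblinding, voluntary exit and failure to complete follow-up. For these patients the reason is recorded and "the last data would be included in data analysis".

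Two notes qualify the list. Note 1 reads: "Patients cured in a course of treatment are not regarded as cases for withdrawal". Note 2 concerns patients who leave for poor efficacy after 14 days. They "are regarded as not recovered but not withdrawn, and they would be included in the Full Analysis Set (FAS") and also in the per-protocol set (PPS).

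A separate list, Dropout of participants, has four entries: misdiagnosis, "Using forbidden drugs or treatments in the course of the trial", taking no medication, and "No evaluable records after medication". It attaches no analysis consequence to any of them.

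Data analysis then says: "Statistical analysis will be conducted based on an intention-to-treat (ITT) principle". The full analysis set (FAS) is "All subjects who were treated with at least one dose of the study drug and had at least one clinical observation after starting the treatment". The PPS is treated patients without major deviations. Scores are analysed as change from baseline to the end of treatment. IBS-QOL and IBS-SSS are the primary outcomes.

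**The concern.** The article fixes a rule here, so this is not a detail left to an analysis plan. Taken with an analysis of change to the end of treatment, the rule puts a score from the time of leaving where a Day 28 score should stand. No other method for missing scores appears.

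Disease progression, poor efficacy, allergic reaction and serious adverse events are all linked to outcome or to drug. If the drug works, or causes reactions, the two arms need not lose patients at the same rate or time. If scores improve over the 28 days, an early score understates what a patient would have shown at Day 28. The arm with more or earlier leavers is then marked down more.

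A second question is who is analysed. A patient who took study drug, had an observation and also used a forbidden drug meets the FAS definition, yet is labelled a dropout. Two of the other three dropout entries (no medication, no evaluable records) describe patients whom the FAS definition excludes. That makes exclusion of the whole list a plausible reading. Forbidden-drug use happens after randomisation and may differ by arm.

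**Working it through.** **Inputs from the article.** Allocation is 330 to 110, and the planned drop-out is 15% overall (Sample size calculation). No rate per arm, no expected score change and no standard deviation is given, so there is no figure of the plan's own to reproduce on this point.

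**Assumptions.** Mean improvement by Day 28 is M_A on active and M_P on placebo, in points. Leavers would have reached their arm's mean improvement by Day 28, but their last score shows only a fraction f of it. I take f = 0.5 (half the improvement) and f = 0 (none). The proportions leaving are d_A and d_P.

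**Formula.** Apparent difference = M_A × [1 − d_A(1 − f)] − M_P × [1 − d_P(1 − f)]. Overall loss = (330 d_A + 110 d_P)/440.

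**No true effect (M_A = M_P = 100).** The formula reduces to 100 × (1 − f) × (d_P − d_A).

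| Active / placebo leaving | Overall loss | f = 0.5 | f = 0 |
|---|---|---|---|
| 15% / 15% | 15% | 0 | 0 |
| 10% / 30% | (33 + 33)/440 = 15% | +10 | +20 |
| 30% / 10% | (99 + 11)/440 = 25% | −10 | −20 |
| 12% / 24% | (39.6 + 26.4)/440 = 15% | +6 | +12 |
| 18% / 6% | (59.4 + 6.6)/440 = 15% | −6 | −12 |

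The 30%/10% row swaps the rates of the 10%/30% row, but at 3:1 allocation it implies 25% loss overall, above the planned 15%. The last two rows hold the overall loss at 15% in both directions. Solving 0.75 d_A + 0.25 d_P = 0.15 with d_A − d_P = 0.12 gives 18% and 6%.

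**True difference of 30 (M_A = 100, M_P = 70).**

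- 15%/15%, f = 0.5: 100 × 0.925 − 70 × 0.925 = 92.5 − 64.75 = 27.75.
- 15%/15%, f = 0: 85 − 59.5 = 25.5.
- 10%/30%: 95 − 59.5 = 35.5 (f = 0.5), and 90 − 49 = 41 (f = 0).
- 30%/10%: 85 − 66.5 = 18.5 (f = 0.5), and 70 − 63 = 7 (f = 0).

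Equal leaving therefore gives no bias when there is no effect, but shrinks a real one. Unequal leaving moves the estimate either way.

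**Does Note 2 repair this?** It assigns a category, not recovered, which suits the response classes built on percentage symptom score reduction, a secondary outcome. It supplies no IBS-SSS or IBS-QOL value, so the primary scores of these patients remain unspecified.

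**Dropout list against the FAS definition.** With one dose and one later observation, a forbidden-drug user or a misdiagnosed patient is in the FAS as defined. The dropout list neither confirms nor denies this.

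**The case against.** Much of what a reader might infer goes further than the text.

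- *Last-value use breaches intention to treat.* It does not. It keeps withdrawn patients in the analysis, and the weakness lies in the value assigned to them.
- *Treated patients are removed.* The dropout list does not say so, and the FAS definition would keep those with a dose and an observation. Misdiagnosis is also an eligibility error, not conduct after randomisation. What stands is that the two sections are not reconciled.
- *Patients cured mid-course have a good score carried forward.* The last-data sentence concerns withdrawn patients, and Note 1 says that cured patients are not withdrawals. Nothing says that their Day 28 assessment is skipped.
- *The standard error is too small.* This is a general criticism of single imputation. Nothing in the article allows it to be shown here.
- *False-positive findings in favour of the drug are to be expected.* With 12%/24% leaving, f = 0.5 and an assumed SD of 90, the spurious 6 points over a standard error of 90 × √(1/330 + 1/110) = 9.91 do raise two-sided rejection to about 9.3%. But an inert drug gives no evident reason for twice the leaving on placebo, and allergic reactions or adverse events would more naturally raise leaving on active. The 18%/6% row has the same size with the opposite sign.

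It is also fair to say that the last-value term never appears, and that sensitivity analyses may sit in an analysis plan not shown. Neither answers the main point: the article states a rule for these patients, and its natural reading is a weak one for the primary scores.

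**Conclusion.** The point holds in a limited form. The last-data rule, read as last-value substitution, is a poor choice for the primary scores because withdrawal is partly driven by outcome and drug. The sign of the bias depends on which arm leaves more or earlier, and its size cannot be known from the article. In the illustration it runs from −20 to +20 per 100 points of improvement when there is no effect. Equal 15% leaving takes 2.25 to 4.5 points off a true 30.

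These figures rest on assumed rates per arm, on leavers showing none to half of the improvement, and on leavers otherwise matching their arm by Day 28. If leavers would in truth have stayed at their last score, the bias would vanish. Separately, the FAS status of treated, evaluable dropouts is ambiguous. This is a change that should be made, not a fault that invalidates the trial.

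**What to change.** 1. Replace the last-data rule for IBS-SSS and IBS-QOL. Analyse the FAS by a mixed model for repeated measures, or by multiple imputation if no visit between baseline and the end of treatment records these scores (the schedule figure is not shown). Keep last-value substitution as a sensitivity analysis only. The new methods make assumptions too, chiefly that leaving is explained by the data observed, but they do not hold a leaver at the last score.
2. Ask patients who stop early, where they agree, to complete both questionnaires at the end-of-treatment time point.
3. Say how the primary scores are handled for the poor-efficacy leavers of Note 2, for whom only a response category is given now.
4. Reconcile Dropout of participants with Data analysis: state that treated, evaluable patients who used forbidden drugs or were misdiagnosed stay in the FAS and are removed from the PPS only.

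The cost is a few sentences of text, modest extra programming, and the effort of following early stoppers for two questionnaires.
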